## Randomization and Blinding

1) Methods of assignment

The randomization manager will implement random assignment in accordance with the randomization procedure. When assigning NPC-12T placebo, the randomization manager will specify three types of dosage: reduction, increase, or no change in dosage. In specifying reduction or increase, specific visit(s) (V7 to V11) when the change in dosage is to be implemented will be indicated. The randomization manager will generate and store a randomization schedule, which is to be concealed. The randomization manager will generate prescription schedules containing information on assignment for respective subjects and specification for change in dosage of NPC-12T placebo tablets. The information for respective subjects will be sealed separately. The prescription schedules will be stored by an unblinded doctor. The randomization manager will store the randomization schedule in strict concealment until the time when the blind is permitted to be broken. When the unblinded doctor makes judgment on dosage change for a subject based on trough concentration measurements (V7 to V11), the doctor will unblind the prescription schedule for the subject in question and check the criteria for dosage change. The prescription schedule will be placed in concealment again immediately after the check. The unblinded doctor will keep a record every time the prescription schedule is unblinded or concealed. The randomization manager will generate two sets of emergency key codes when the assignment is made, which will be kept strictly in concealment by the randomization manager and the emergency contact center (the administrative office supporting clinical trial: Keio University Hospital Clinical and Translational Research Center) until the blind is authorized to be broken.

2) Indistinguishability

The randomization manager will verify the indistinguishability of medications and packages before random assignment and after the end of the trial.

3) Maintenance of blindness during the trial

With regard to the blood concentration of sirolimus, any person involved in the trial, with the exception of the unblinded doctor and unblinded clinical research coordinators (CRCs), will follow the procedures for prescription of investigational products to ensure blindness to the test results is maintained. The test results will be reported to the Independent Data Monitoring Committee and the principal investigator, however, after the blind is broken or if the principal investigator so directs in case of emergency. The unblinded CRCs will assist in the work of the unblinded doctor and make sure that the dosage change based on trough concentration measurements is appropriately instructed.

## Procedure for Concealing and Unblinding Randomized Code

The randomization manager will conceal and store the randomization schedule (randomized code) after the random assignment, and unblind it after the database is locked and the trial is completed.

Two sets of emergency key codes will be generated, which will be concealed by the randomization manager. The randomization manager and the emergency contact center (the administrative office supporting clinical trial: Keio University Hospital Clinical and Translational Research Center) will keep them in strict concealment until the appropriate time when the blind is permitted to be broken. When a serious adverse event or other situation demands urgent need for the principal investigator or subinvestigator to access information on assigned treatment to determine treatment of the subject, or when discovery of subject’s pregnancy requires revelation of assigned treatment, the principal investigator will determine whether the code should be partially unblinded. If the principal investigator deems it necessary to unblind the code assigned to the subject in question, the emergency contact center will be requested to allow partial unblinding of the randomization code (emergency key code). The partial unblinding of the emergency key code will be conducted in accordance with the procedure manual for unblinding.

The emergency contact center will communicate the unblinded information to the principal investigator. If partial unblinding is performed, the principal investigator will document justification for unblinding and the extent to which the information is made available.

# Administration of Investigational Products

Figure 1 Dosing Protocol

Phase I (single-blind): NPC-12T placebo tablets for 3 months (12 weeks)

Phase II (double-blind): NPC-12T active substance tablets or NPC-12T placebo tablets for 6 months (24 weeks)

[Dosage at the outset of the trial]

Subjects weighing less than 40 kg will take one 1-mg tablet orally once every other day.

Subjects weighing 40 kg or more will take one 1-mg tablet orally once per day.

The investigational products are to be taken before sleep.

The bodyweight measured at V1 will be referred to in determining dosage throughout the trial.

<Rationale for the dosing time>

The package insert of Rapamune 1 mg tablets was referred to when setting the dosing time. The insert cites reports that state administration of the tablet after a high-fat meal increased the blood concentration of sirolimus. To reduce effects of high-fat meals, the dosing time of the investigational products is set to be before sleep.

[Prescription of the investigational products]

In Phase I (V1, V2, V3, and V4) and Phase II (V5 and V6), the principal investigator or subinvestigator will prescribe investigational products in accordance with the dosage at the start of the trial described above.

In Phase II (V7, V8, V9, V10, and V11), the unblinded doctor will instruct the principal investigator and subinvestigators on the prescription of the investigational product based on the criteria for dosage change. The principal investigator or subinvestigator will make a judgment on whether dosage reduction is required or dosage increase is permissible, taking account of subjects’ safety, including risks of adverse events. If the conditions are deemed appropriate, the principal investigator or subinvestigator will prescribe the investigational products as instructed by the unblinded doctor. The unblinded doctor will provide instructions to the principal investigator or subinvestigator in accordance with the trough concentration measurements and the prescription schedule generated by the randomization manager. The trough concentration measurements and the prescription schedule are not to be disclosed to any person except the unblinded CRCs until the end of the trial, and will be kept securely locked in a cabinet accessible only to the unblinded doctor.

[Criteria for dosage change]

From Phase II, the dosage will be determined taking account of the trough concentration measurements from the last visit (V6, V7, V8, V9, and V10) and occurrence of adverse events.

The unblinded doctor will provide instructions to the principal investigator or subinvestigator on prescription of the investigational products based on the trough concentration measurements at visits.

The principal investigator or subinvestigator will make a judgment on whether dosage reduction is required or dosage increase is permissible before prescribing, with due consideration for the subjects’ safety, such as risks of adverse events.

In this trial, the therapeutic range of the trough concentration following the administration of NPC-12T active substance is set to be 2.5 to 7.5 ng/mL. The trough concentration at the last visit below 2.5 ng/mL will be considered to be suitable for dosage increase, and that exceeding 7.5 ng/mL for dosage reduction.

Dosage increase for NPC-12T active substance will be permitted only if the principal investigator or subinvestigator deems it appropriate from the viewpoint of subject safety. The unblinded doctor will instruct the principal investigator or subinvestigator to prescribe the investigational products not exceeding two 1-mg tablets per day (i.e., 2 mg/day), administered orally.

The reduced dosage of NPC-12T active substance should be no less than one 1-mg tablet every three days, administered orally. If further reduction is required, administration of the investigational product to the subject will be discontinued.

As dosage adjustment according to trough concentration is unsuitable for the NPC-12T placebo arm, one of increase, reduction, or no change in dosage is specified for the placebo arm at the time of assignment of the investigational products. At the same time, the randomization manager will designate the visits for dosage change for the placebo arm.

Dosage increase for NPC-12T placebo will be permitted only if the principal investigator or subinvestigator deems it appropriate from the viewpoint of subject safety. When dosage increase is specified in the prescription schedule, the unblinded doctor will instruct the principal investigator or subinvestigator to prescribe a dosage level at one tier higher.

If the prescription schedule specifies reduction, the unblinded doctor will instruct the principal investigator or subinvestigator regarding dosage reduction for NPC-12T placebo. The dosage level will be lowered by one tier at a time. The reduced dosage must be no lower than one 1-mg tablet every three days, administered orally. If further reduction is required, administration of the investigational products will be discontinued.

If the principal investigator or subinvestigator determines further reduction is required, administration of the investigational products will be discontinued.

The unblinded doctor will provide instructions to the principal investigator or subinvestigator on prescription in accordance with the specified dosage change in the prescription schedule. The decision by the principal investigator or subinvestigator on permission for dosage increase and reduction shall take precedence over the specification in the prescription schedule, i.e., if the principal investigator or subinvestigator specifies reduction, and the prescription schedule states increase, reduction should be adopted.

[Acceptable change in dosage]

The amounts of investigational products to be administered can be increased or decreased to one of the following dosages:

A. Two 1-mg tablets, once per day, administered orally

B. One 1-mg tablet, once per day, administered orally

C. One 1-mg tablet, once every other day, administered orally

D. One 1-mg tablet, once every three days, administered orally

[Dosage reduction or increase]

When dosage is to be increased, the dosage level should be raised by one tier at a time: Subjects weighing 40 kg or over will follow the change from B to A. Subjects weighing below 40 kg will follow the change from C to B to A.

When dosage is to be reduced, the dosage level should be lowered by one tier at a time, from A to B to C to D. If the current level for a subject is B, for example, C will be applied in the next reduction. If further reduction below D is required, administration of the investigational products to the subject will be discontinued.

[Suspension or reduction of administration of investigational products due to adverse events]

・Unacceptable adverse events or exacerbation considering the safety of the subject

・Unacceptable abnormal observations in clinical tests considering the safety of the subject

If a situation described above arises, dosing will be suspended until the relevant symptoms abate. The dosage will then be reduced by one tier at a time from A to B to C to D. If the sirolimus dosage is 1 mg/day every three days, administered orally, which corresponds to D, the dosing will be discontinued, and follow-up observations will be performed one month after that, before discontinuation of the patient’s participation in the trial, in principle.

The initial administration of investigational products in Phase II for respective subjects shall not be performed on the same day.

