| 1. Dosage of the Investigational Products     Dosing Protocol  Phase I (single-blind): NPC-12T placebo tablets for 3 months (12 weeks)  Phase II (double-blind): NPC-12T active substance tablets or NPC-12T placebo tablets for 6 months (24 weeks)  [Dosage at the outset of the trial]  Subjects weighing less than 40 kg will take one 1-mg tablet orally once every other day.  Subjects weighing 40 kg or more will take one 1-mg tablet orally once per day.  The investigational products are to be taken before sleep.  The bodyweight measured at V1 will be referred to in determining dosage throughout the trial.  [Prescription of the investigational products]  In Phase I (V1, V2, V3, and V4) and Phase II (V5 and V6), the principal investigator or subinvestigator will prescribe investigational products in accordance with the dosage at the start of the trial described above.  In Phase II (V7, V8, V9, V10 and V11), an unblinded doctor will instruct the principal investigator and subinvestigators on the prescription of the investigational product based on the criteria for dosage change. The principal investigator or subinvestigator will make a judgment on whether dosage reduction is required or dosage increase is permissible, taking account of subjects’ safety, including risks of adverse events. If the conditions are deemed appropriate, the principal investigator or subinvestigator will prescribe the investigational products as instructed by the unblinded doctor. The unblinded doctor will provide instructions to the principal investigator or subinvestigator in accordance with the trough concentration measurements and the prescription schedule generated by the randomization manager. The trough concentration measurements and the prescription schedule are not to be disclosed to any person except the unblinded CRCs until the end of the trial, and will be kept securely locked in a cabinet accessible only to the unblinded doctor.  [Criteria for dosage change]  From Phase II, the dosage will be determined taking account of the trough concentration measurements from the last visit (V6, V7, V8, V9, and V10) and occurrence of adverse events.  The unblinded doctor will provide instructions to the principal investigator or subinvestigator on prescription of the investigational products based on the trough concentration measurements at visits.  The principal investigator or subinvestigator will make a judgment on whether dosage reduction is required or dosage increase is permissible before prescribing, with due consideration for the subjects’ safety, such as risks of adverse events.  In this trial, the therapeutic range of the trough concentration following the administration of NPC-12T active substance is set to be 2.5 to 7.5 ng/mL. The trough concentration at the last visit below 2.5 ng/mL will be considered to be suitable for dosage increase, and that exceeding 7.5 ng/mL for dosage reduction.  Dosage increase for NPC-12T active substance will be permitted only if the principal investigator or subinvestigator deems it appropriate from the viewpoint of subject safety. The unblinded doctor will instruct the principal investigator or subinvestigator to prescribe the investigational products not exceeding two 1-mg tablets per day (i.e., 2 mg/day), administered orally.  The reduced dosage of NPC-12T active substance should be no less than one 1-mg tablet every three days, administered orally. If further reduction is required, administration of the investigational product to the subject will be discontinued.  As adjustment of dosage according to trough concentration is unsuitable for the NPC-12T placebo arm, one of increase, reduction, or no change in dosage is specified for the placebo arm at the time of assignment of the investigational products. At the same time, the randomization manager will designate the visits for dosage change for the placebo arm.  Dosage increase for NPC-12T placebo will be permitted only if the principal investigator or subinvestigator deems it appropriate from the viewpoint of subject safety. When dosage increase is specified in the prescription schedule, the unblinded doctor will instruct the principal investigator or subinvestigator to prescribe a dosage level at one tier higher.  If the prescription schedule specifies reduction, the unblinded doctor will instruct the principal investigator or subinvestigator regarding dosage reduction for NPC-12T placebo. The dosage level will be lowered by one tier at a time. The reduced dosage must be no lower than one 1-mg tablet every three days, administered orally. If the principal investigator or subinvestigator determines further reduction is required, administration of the investigational products will be discontinued.  The unblinded doctor will provide instructions to the principal investigator or subinvestigator on prescription in accordance with the specified dosage change in the prescription schedule. The decision by the principal investigator or subinvestigator on permission for dosage increase and reduction shall take precedence over the specification in the prescription schedule, i.e., if the principal investigator or subinvestigator specifies reduction, and the prescription schedule states increase, reduction should be adopted.  [Acceptable change in dosage]  The amounts of investigational products to be administered can be increased or decreased to one of the following dosages:  A. Two 1-mg tablets, once per day, administered orally  B. One 1-mg tablet, once per day, administered orally  C. One 1-mg tablet, once every other day, administered orally  D. One 1-mg tablet, once every three days, administered orally  [Dosage reduction or increase]  When dosage is to be increased, the dosage level should be raised by one tier at a time: Subjects weighing 40 kg or over will follow the change from B to A. Subjects weighing below 40 kg will follow the change from C to B to A.  When dosage is to be reduced, the dosage level should be lowered by one tier at a time, from A to B to C to D. If the current level for a subject is B, for example, C will be applied in the next reduction. If further reduction below D is required, administration of the investigational product to the subject will be discontinued.  [Suspension or reduction of administration of investigational products due to adverse events]  ・Unacceptable adverse events or exacerbation considering the safety of the subject  ・Unacceptable abnormal observations in clinical tests considering the safety of the subject  If a situation described above arises, dosing will be suspended until the relevant symptoms abate. The dosage will then be reduced by one tier at a time from A to B to C to D. If the sirolimus maintenance dose is 1 mg per day every three days, administered orally, which corresponds to D, the dosing will be discontinued, and follow-up observations will be performed one month after that, before discontinuation of the patient’s participation in the trial, in principle.  The initial administration of investigational products in Phase II for respective subjects shall not be performed on the same day. |

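### Below 40 kg, the trough criterion permits a second dose increase at V8 on a level drawn before the first increase took effect

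*Protocol*

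**What the plan says.** Under Administration of Investigational Products, the starting dose is fixed at V5 and V6, and changes are possible at five later visits: "In Phase II (V7, V8, V9, V10, and V11), the unblinded doctor will instruct the principal investigator and subinvestigators on the prescription". The criteria for dosage change tie these five decisions to five earlier samples: "trough concentration measurements from the last visit (V6, V7, V8, V9, and V10) and occurrence of adverse events". The Protocol Summary has the same rule: "the dosage will be determined taking account of the trough concentration measurements from the last visit (V6, V7, V8, V9, and V10". The target range is 2.5 to 7.5 ng/mL, and the increase criterion is: "The trough concentration at the last visit below 2.5 ng/mL will be considered to be suitable for dosage increase". A last-visit level above 7.5 ng/mL is the matching criterion for a reduction.

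Three further statements matter:
- Timing of the dose: "The investigational products are to be taken before sleep".
- Upward path for light subjects, one tier at a time: "Subjects weighing below 40 kg will follow the change from C to B to A".
- Who decides, under Randomization and Blinding: "the unblinded doctor makes judgment on dosage change for a subject based on trough concentration measurements (V7 to V11". The investigator must also find an increase acceptable for the subject's safety, but is not shown the levels.

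No sentence asks for a minimum time on a dose, or for a level drawn on the current dose, before the next increase.

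**The concern.** Each decision uses the level from the visit before. If the dose was changed at that visit, the level belongs to the old dose. For a subject who starts on tier C and has two upward steps available, both steps can rest on tier-C levels. The second step is then taken without knowing what the first achieved.

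Safety and tolerability are the primary endpoints, enrolment starts at age seven, and the subjects concerned are the lightest. At stake is avoidable time above the protocol's own range at four times the starting dose, when twice that dose would have been enough.

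**Working it through.** **Inputs from the protocol**
- Visits V5 to V12 at weeks 12, 14, 16, 20, 24, 28, 32, 36 (Table 1); sirolimus sampled at each (Blood Concentration of Sirolimus).
- Mean daily dose: C = 0.5 mg, B = 1 mg, A = 2 mg. Range 2.5 to 7.5 ng/mL.
- Decision at a visit uses the level from the previous visit. That level reflects the dose taken before the previous visit, because dosing is at bedtime.

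**Assumptions, not in the protocol**
- Trough proportional to mean daily dose, at steady state at each visit.
- Every change that counts as suitable is made.

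**Step 1: the sequence for a tier-C trough of 2.0 ng/mL** (so 4.0 on B, 8.0 on A)

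| Visit (week) | Level drawn | Level used | Dose from this visit |
|---|---|---|---|
| V6 (14) | 2.0 on C | none | C |
| V7 (16) | 2.0 on C | V6: 2.0 on C | B |
| V8 (20) | 4.0 on B | V7: 2.0 on C | A |
| V9 (24) | 8.0 on A | V8: 4.0 on B | A |
| V10 (28) | 8.0 on A | V9: 8.0 on A | B |
| V11 (32) | 4.0 on B | V10: 8.0 on A | C |
| V12 (36) | 2.0 on C | none | end |

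Below range: weeks 12–16 and 32–36, 8 weeks. Within: weeks 16–20 and 28–32, 8 weeks. Above: weeks 20–28, 8 weeks. With visit windows of 7 days at V8 and V10, the time on A is 56 ± 14 days, i.e. 6 to 10 weeks.

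**Step 2: limits under proportionality**, with tier-C trough x, so 2x on B and 4x on A
- B is in range, so the second step is unneeded: 2x ≥ 2.5, x ≥ 1.25.
- A exceeds the range: 4x > 7.5, x > 1.875.
- A is still below range: 4x < 2.5, x < 0.625 (about 0.63).

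**Step 3: weeks below/within/above, as written and if increases wait for a level on the current dose**

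| x on C | on B, A | As written | With the wait |
|---|---|---|---|
| 0.4 | 0.8, 1.6 | 24/0/0, A from week 20 | 24/0/0, A from week 24 |
| 1.0 | 2.0, 4.0 | 8/16/0 | 12/12/0 |
| 1.5 | 3.0, 6.0 | 4/20/0 | 4/20/0 |
| 2.0 | 4.0, 8.0 | 8/8/8 | 4/20/0 |
| 2.4 | 4.8, 9.6 | 8/8/8 | 4/20/0 |

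In the upper band 12 weeks out of range are avoidable. The 8 above come from the lagged increase. The last 4 below also need the lagged reduction at V11: with increases as written but reductions waiting, the result is 4/12/8.

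**Step 4: sensitivity to the dose-to-trough relation.** The protocol does not fix on which day of the every-other-day cycle the sample is drawn. For one-compartment kinetics with k = ln 2 / half-life, B:C = 1 + e^(24k) when sampled at the end of 48 h and 1 + e^(−24k) when sampled after a dosing night. A:C is twice that, and the lower limit of the overshoot band is 7.5/(A:C). Half-lives are assumed.

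| Half-life (h) | End of 48 h: A:C, lower limit, width | After a dosing night: A:C, lower limit, width |
|---|---|---|
| 40 | 5.03, 1.49, 1.01 | 3.32, 2.26, 0.24 |
| 60 | 4.64, 1.62, 0.88 | 3.52, 2.13, 0.37 |
| 80 | 4.46, 1.68, 0.82 | 3.62, 2.07, 0.43 |

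A tier-C trough of 2.3 gives 8/8/8 as written and 4/20/0 with the wait in all six cases. A trough of 2.0 sampled after a dosing night does not overshoot at any of the three half-lives. The band vanishes if A:C is 3 or less. Two increases are needed below 2.5/(B:C): 0.99, 1.08, 1.12 at the end of 48 h, or 1.51, 1.42, 1.38 after a dosing night.

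**The case against.** The rule is permissive. The dose is set with the levels taken into account, and a low level only makes an increase suitable. The unblinded doctor holds both the levels and the assignment, so can see that the V7 sample was drawn on tier C. Steps are one tier at a time, capped at 2 mg/day, and adverse events or abnormal tests lead to suspension and reduction. The separate prescription procedures mentioned under Randomization and Blinding are not shown and may already contain a wait. Tier A is a planned dose for these subjects, and faster titration within 24 weeks is a defensible aim.

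Most of this stands and limits the point. A reader might infer that the protocol requires the second increase; it does not. The gap remains because the only written criterion points towards the increase, and the investigator's safety check is made without sight of the levels. Laboratory cover is also thin at that point: Table 1 has no clinical laboratory tests at V9, so the first on tier A fall at V10, and the Laboratory Tests section omits V10 from its list.

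The objection on cost also stands. The wait delays everyone who needs two increases, a wider range of troughs than the band it helps. That includes subjects below 0.63 on C, who stay below range even on A. For a tier-C trough of 0.4, it means weeks 20–24 at 0.8 instead of 1.6 ng/mL, and 0.8 is under the 0.9 ng/mL in vitro minimum given in the background.

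**Conclusion.** The point holds as a minor weakness in a stated rule. The criterion, followed as written, can take a subject below 40 kg from C to A by V8 on two tier-C levels. That sequence follows from the text and needs no pharmacokinetic assumption. Its size does: under proportionality and full application of the criterion, about 8 avoidable weeks above 7.5 ng/mL for tier-C troughs above 1.875 and below 2.5, with a narrower or wider band under other kinetics.

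The number affected is unknown and may be zero: 12 active subjects are planned, and only those below 40 kg at V1 and inside the band count. Decisions at V7, decisions with no change at the visit before, and increases from the starting dose at 40 kg or more (one upward step) are not touched.

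Three stronger readings are not supported:
- That levels above 7.5 ng/mL are shown to be toxic. The protocol presents this as the top of a therapeutic range, and passing it only makes a reduction suitable.
- That efficacy results are damaged. The below-range levels in the overshoot band are about 1.5 to 2.5 ng/mL, above the in vitro minimum of 0.9.
- That the placebo schedules are faulty. They are not shown, and no defect is demonstrated.

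**What to change.** Add one sentence to the criteria for dosage change in the Protocol Summary and in Administration of Investigational Products: a trough-driven increase requires a trough below 2.5 ng/mL measured on the current dose, so none is made at the visit immediately after a dose change. State that reductions for adverse events or safety remain unrestricted. If the separate prescription procedures already contain this wait, a cross-reference is enough.

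Placebo changes are pre-specified ("specific visit(s) (V7 to V11) when the change in dosage is to be implemented will be indicated"), so check that their pattern stays consistent with what the amended rule allows in the active arm.

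No visits or samples are added. The price is that every subject needing two increases reaches tier A at V9 (week 24) instead of V8 (week 20). Where tier A brings the level into range (tier-C troughs of about 0.63 to 1.25 under proportionality), this means 12 instead of 8 weeks below it. Below 0.63 the higher dose simply starts four weeks later. With safety as the primary endpoint and enrolment from age seven, four weeks' delay is the more acceptable error, but that is a judgment the investigators should make knowingly.

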### Causality Assessment

Causality is categorized into “related” or “unrelated,” which are defined below. An adverse event that is considered to be “related” to the investigational products is regarded as a side effect.

[Criteria for judging causality]

| Causality | Description |
| --- | --- |
| Related | There is a reasonable possibility that the adverse event is related to the investigational products. |
| Unrelated | Conditions other than the above. |

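### Placebo sham dose schedules run in one direction only, so a reversal made up solely of the unblinded doctor's instructions identifies sirolimus to the blinded investigator

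*Protocol*

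**What the plan says.** The protocol describes the placebo mechanism in three places. Under Administration of Investigational Products, [Criteria for dosage change], it says that "one of increase, reduction, or no change in dosage is specified for the placebo arm at the time of assignment of the investigational products"; the Protocol Summary repeats this. Randomization and Blinding says that "the randomization manager will specify three types of dosage: reduction, increase, or no change in dosage" and adds: "In specifying reduction or increase, specific visit(s) (V7 to V11) when the change in dosage is to be implemented will be indicated".

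The active rule differs. The dose takes account of "trough concentration measurements from the last visit (V6, V7, V8, V9, and V10) and occurrence of adverse events", which gives five decisions, at V7 to V11. Each can go either way: "The trough concentration at the last visit below 2.5 ng/mL will be considered to be suitable for dosage increase, and that exceeding 7.5 ng/mL" for reduction. Changes are one tier at a time over four tiers, A (highest) to D. Subjects of 40 kg or more start at B and those below 40 kg at C; on the way up, "Subjects weighing below 40 kg will follow the change from C to B to A". Nothing bars a later move in the opposite direction.

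The blinded investigator sees every instruction: if conditions are judged appropriate, "the principal investigator or subinvestigator will prescribe the investigational products as instructed by the unblinded doctor". The investigator's own decision on an increase or reduction overrides the schedule, and reductions after adverse events apply in both arms.

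Under Causality Assessment, an adverse event judged related "to the investigational products is regarded as a side effect". Side effects are among the primary endpoints.

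**The concern.** Sham changes serve only to make the stream of instructions uninformative about the arm. They do so only if the placebo arm can show every pattern that the active arm can show. Here a whole class of patterns, those with both an instructed increase and an instructed reduction, is closed to placebo. The investigator works from the protocol that states this rule and can draw the inference.

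What is exposed is mainly the causality judgment, for which the protocol names no assessor outside the investigator team. That judgment defines side effects. Under Definition of Adverse Events it also decides whether an exacerbation of the primary disease counts as an adverse event at all. The trial-discontinuation criteria and the monitoring committee's criteria refer to it too. Certain identification by this route can happen only in the active arm, so any resulting bias is one-sided.

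**Working it through.** The protocol states no figure on this point, so there is none to reproduce.

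**1. Which patterns are covered.** Inputs: four tiers, start at B or C, five decisions (V7 to V11), each up, unchanged or down by one tier.
- Sequences that stay within A to D: 144 from either start.
- With no reversal, from B: 1 unchanged + 5 with a single increase + (5 + 10) with one or two reductions = 21. From C the count mirrors this and is also 21.
- With both directions: 144 − 21 = 123.

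A literal sham schedule can produce only the 21. This counts possible patterns and says nothing about how likely each is.

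**2. What an instructed reversal tells the investigator.** Let p and q be the probabilities of an instruction-only reversal on active and placebo. With 12 active and 4 placebo subjects:

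P(active | reversal) = 12p / (12p + 4q)

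- Before any reversal: 12/16 = 75%.
- As written, q = 0: 12p/12p = 100%.
- With q = p: 12/16 = 75%, no information.

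**3. Can the active rule produce one?** Assume that trough is proportional to average daily dose (C 0.5 mg, B 1 mg, A 2 mg, D 1/3 mg), that it is stable by the next visit, and that every instruction is followed. Each decision uses the previous visit's trough.

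Below 40 kg, starting at C with trough c between 1.875 and 2.5 ng/mL:

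| Decision | Trough used | Reflects | Value (ng/mL) | Instruction |
|---|---|---|---|---|
| V7 | V6 | C | c, below 2.5 | up to B |
| V8 | V7 | C (drawn before the change) | c, below 2.5 | up to A |
| V9 | V8 | B | 2c = 3.75 to 5 | none |
| V10 | V9 | A | 4c = 7.5 to 10 | down to B |
| V11 | V10 | A | 4c = 7.5 to 10 | down to C |

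The lower limit is 7.5/4 = 1.875. The lag of one visit between measurement and prescription creates the overshoot; no random variation is needed.

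40 kg or more, starting at B with trough b:
- b below 2.5: up to A, then 2b is below 5, so no reduction follows.
- b above 7.5: down to C and then D; at D the trough is b/3, above 2.5, so no increase follows.

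Under the same assumptions there is no reversal from B.

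**4. Sensitivity to within-subject variation.** All inputs here are assumptions: median starting trough 1.5 to 6 ng/mL, between-subject log-SD 0.45, within-subject CV 0 to 50%. Simulated probability of a reversal per active subject:

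| Start | CV 0 | CV 20% to 50% |
|---|---|---|
| B | 0 | about 1% to 44% |
| C | about 2% to 25% | about 4% to 47% |

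The width of these ranges shows that the protocol does not determine the rate.

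**The case against.** A reader might infer that any reversal gives the arm away. The protocol does not support that. A placebo subject with a scheduled increase may later be reduced by the investigator for safety, and one reduced for safety may later receive a scheduled increase. Both are reversals on placebo. Only a reversal with no investigator-initiated change is diagnostic. The investigator can tell the two apart, because the safety decisions are the investigator's own.

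A reader might also infer that some definite share of the 12 active subjects will be unblinded. With no concentration distribution in the protocol, no share can be given. If all subjects weigh 40 kg or more and kinetics are stable, the number is zero.

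Other points on that side:
- Neither placebo sentence expressly forbids different directions at different visits, and a separate randomization procedure is not shown. One direction per subject is still the natural reading of one of three types.
- Instructions are not automatic: an out-of-range trough is treated as suitable for change, adverse events are weighed, and increases need the investigator's agreement. So the path in the table is possible, not certain.
- On that path the first reversing instruction comes at week 28, after 16 of the 24 Phase II weeks. Causality judgments already made are unaffected.
- The investigator already holds a 75% prior for active treatment.
- Home audiometry, the daily questionnaire and the dizziness inventory are completed by subjects, and audiometric episodes follow a fixed 10 dB rule. Adverse events are summarized by arm with confidence intervals, with no between-arm test planned.

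These points limit the size and timing of the leak. They do not remove it.

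**Conclusion.** The point holds in a limited form. Taking the placebo rule as written, an instruction-only reversal has probability zero on placebo and identifies active treatment with certainty. That result needs only the literal reading and the investigator's knowledge of the rule, not any pharmacokinetic assumption.

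Whether such reversals happen does depend on kinetics. With dose-proportional, stable troughs and every instruction followed, they occur below 40 kg in a starting-trough band 0.625 ng/mL wide (2.5 − 1.875). At 40 kg or more they require within-subject variation, which the protocol does not quantify. The number of subjects affected is therefore unknown and may be zero. The consequence is concentrated in causality judgments made after the reversal. This is a defect in the blinding procedure that should be corrected; it does not invalidate the trial.

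**What to change.** In the Protocol Summary (dosage section), in Randomization and Blinding, and in Administration of Investigational Products, [Criteria for dosage change], state that a placebo prescription schedule may contain instructions in both directions at different visits. Pattern them on sequences that the active rule can produce in the same weight class. The randomization manager could pre-generate them by applying the existing rule to simulated concentrations. The investigator's safety precedence and all active-arm dose rules stay as they are. If the sponsor already intended mixed directions within a subject, the wording that assigns one of three types should be corrected to say so.

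The cost is matching edits in three places, a revised randomization procedure, and a few more sham changes in up to 4 placebo subjects. No visits are added. Generating the sequences requires an assumed concentration distribution, so the match will be approximate, but an approximate match still helps. If placebo reversals were half as frequent as active ones, P(active | reversal) would be 12/(12 + 4 × 0.5) = 86%; if twice as frequent, 12/(12 + 4 × 2) = 60%. Neither is the certainty that the present text allows.
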